Exclusion criteria at the baseline are: diagnosis of (a) a serious mental disorder (e.g., schizophrenia, schizoaffective disorder, other psychotic disorders, bipolar and related disorders, and personality disorders), (b) a chronic disease resulting in functional impairment, or (c) a neurodevelopmental disorder (e.g., autism spectrum disorders and intellectual disability); history of major depression; being under antidepressant medication; alcohol and/or drug addiction; high-risk pregnancy; and fetal malformations. These criteria were defined to ensure that relevant stress-related heterogeneity at the baseline will be reduced in the study. In addition to these exclusion criteria, mother–child dyads will be excluded from the study (after enrolment) in case of preterm birth (less than 37 weeks of gestational age), very-low weight at birth (less than 1500 g), or unexpected newborn malformations.

Randomization will follow the minimization procedure [67] aiming for a balanced sample size for educational level and age groups at the baseline (18–24 years old, 25–34 years old, and 35–40 years old). Random numbers and their assignment will be sealed in envelopes, kept in sequence and opened consecutively by trained researchers as pregnant women are screened for eligibility and enrolled in the study.

The minimum sample size for MAMH@WORK project will be 159, that is 53 women in each group. Attrition rate is considered to be approximately 40% and thus, a total of 225 pregnant women, 75 in each arm, will be enrolled in the study. These calculations are based on a literature review on psychological interventions for PPD prevention, which found mean depression scores (± standard deviation) of intervention and control groups of 11.00 ± 14.63 and 11.52 ± 14.93, respectively, at the final assessment of the study [39]. These sample size calculations assume the average difference between intervention and control arms reported by Dennis and Dowswell [39], considering a 95% confidence interval and a 80% power of the test to detect a difference between depression scores of both arms. This sample size allows for a medium effect size of the intervention to be detected for depression and anxiety scores.

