### 2.5. Statistical Analyses

Statistical analyses will be performed using IBM/SPSS 26.0 (or a more recent version at the time of data analysis) (IBM Corporation, NY, USA) [70] and R Software (R Foundation for Statistical Computing, Vienna, Austria) [71]. For all statistical analyses, the significance level will be set to α = 0.05.

Two strategies for data analysis will be performed: intention-to-treat (ITT) and per-protocol (PP) analyses. ITT considers all participants allocated to arms at the baseline, thus providing a more conservative estimate of the treatment effect, allowing for noncompliance and protocol deviations. In this case, the last observation carried forward method will be used to deal with missing data. PP analysis includes the subset of participants who completed all evaluations. Results from both types of analyses will be reported when comparing control and intervention groups. For effect size estimation, only PP results will be used, since these allow the identification of the treatment effect under optimal conditions, i.e., without major deviations from the protocol. Sensitivity analyses will be carried out to identify potential effects of data strata and missing data on the outcome.

Univariate description of sociodemographic and outcome variables will be performed by providing central tendency (mean and median) and dispersion (standard deviation and range) measures for each moment of data collection. Normality tests (Kolmogorov–Smirnov test or Shapiro–Wilk test) in combination with kurtosis and symmetry analyses will be used to assess the distribution of the variables under study. Levene´s test will be used to assess homoscedasticity. Baseline between-groups comparisons, i.e., control versus intervention groups, will be tested through ANOVA or its non-parametric equivalent (Kruskal–Wallis) for continuous variables, and chi-square test for categorical variables. Mixed model repeated measure (MMRM) analyses will be used for the analyses of main and secondary outcomes, comparing between control and intervention groups and adjusting for relevant covariates (including potential confounding factors). Mediation and moderation analyses will be explored using structural equation modelling. Conceptually and statistically relevant variables will be selected to adjust the models. The size of the intervention effect will be assessed by calculating Cohen’s *d* coefficient [98] Cramer’s V, and odds ratio.

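### The article says 53 women per arm gives 80% power for the cited review's difference, but the figures it quotes give about 5% power, and its medium-effect claim contradicts that basis

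*Protocol article*

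**What the plan says.** Section 2.2 (Sampling Details and Characteristics of the Sample) holds the article's only power justification. It makes four statements.

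- The size: "The minimum sample size for MAMH@WORK project will be 159, that is 53 women in each group". Allowing for about 40% attrition, 225 women (75 per arm) are to be enrolled.
- The source figures, from a literature review of psychological interventions to prevent postpartum depression: "mean depression scores (± standard deviation) of intervention and control groups of 11.00 ± 14.63 and 11.52 ± 14.93, respectively", at final assessment.
- The basis: "These sample size calculations assume the average difference between intervention and control arms reported by" that review, "considering a 95% confidence interval and a 80% power of the test to detect a difference between depression scores of both arms".
- A second description of what the number achieves: "This sample size allows for a medium effect size of the intervention to be detected for depression and anxiety scores".

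Section 2.5 adds that "the significance level will be set to α = 0.05" for all analyses. No numerical effect size, test or sidedness is given for the calculation.

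**The concern.** The difference, both SDs, the power and the resulting n are all printed, so this is not detail that a condensed article may leave to a fuller document. It is a stated calculation that can be checked against its own inputs. Half a point against an SD of nearly 15 is a very small standardised difference, and 53 per arm is a number usually associated with an effect of about half an SD.

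Depression, measured by HADS and EPDS, is among the main outcomes (section 2.4). If the paragraph stands, the trial claims 80% power for the difference found in earlier prevention trials, and the review appears to lend empirical support to a medium effect that its quoted figures do not show. A non-significant result could then be taken as evidence against an effect of the review's size, which the trial has almost no ability to see.

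**Working it through.** **Inputs.** From section 2.2: means 11.00 and 11.52, SDs 14.63 and 14.93, power 80%, 53 per arm, 75 per arm enrolled, attrition about 40%. From section 2.5: alpha 0.05. Assumed: two-sided testing, inferred from the 95% confidence interval (one-sided is also shown).

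**Step 1. Standardised difference.**
Difference = 11.52 − 11.00 = 0.52.
Pooled SD = √[(14.63² + 14.93²)/2] = √218.47 = 14.78.
d = 0.52/14.78 = 0.0352.

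**Step 2. Attempt to reproduce 53 per arm.**
n per arm = 2(z₀.₉₇₅ + z₀.₈₀)²/d² = 2(1.960 + 0.842)²/0.0352² ≈ 12,684 (using unrounded d).
One-sided: 9,991. With SD 14.63 alone: 12,426. With SD 14.93 alone: 12,941.
The stated 53 is not reproduced; the two-sided requirement is 12,684/53 ≈ 239 times larger. For a 0.52-point difference to need only 53 per arm, the SD would have to be about 0.96 (two-sided) or 1.08 (one-sided), not 14.8.

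**Step 3. Power at the stated size for the quoted difference.**
Two-sample t-test, noncentrality d√(n/2) = 0.0352 × √26.5 = 0.181.

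| Reading | Power |
|---|---|
| 53 per arm, two-sided | 5.4% |
| 53 per arm, one-sided | 7.1% |
| 75 per arm, two-sided | 5.5% |
| Both intervention arms pooled against control (106 vs 53) | 5.5% |
| Three-group F-test, N = 159, means 11.00, 11.00, 11.52 | 5.3% |

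Covariate adjustment cannot close the gap. If it scales the required n by (1 − ρ²), bringing 12,684 down to 53 needs ρ = √(1 − 53/12,684) ≈ 0.998.

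**Step 4. Comparison with a medium effect.**
The article attaches no number to it. Taking the conventional d = 0.5 (an assumption), 0.5/0.0352 ≈ 14, so the two sentences describe effects that differ about 14-fold.

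**Step 5. Where 159 might come from.**
A one-way F-test on three groups at the conventional f = 0.25, alpha 0.05 and 80% power needs N = 157.2, which rounds up to 53 per group; power at N = 159 is 80.5%. This is an inference: the article names neither this test nor this effect size.

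**Step 6. What one arm against control can detect** (unadjusted two-sided t-test, alpha 0.05).
Completers under the stated attrition: 75 × (1 − 0.40) = 45 per arm.

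| n per arm | d detectable at 80% power | Power at assumed d = 0.5 |
|---|---|---|
| 45 | 0.60 | 65% |
| 53 | 0.55 | 72% |
| 75 | 0.46 | 86% |

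At 53 per arm, d = 0.55 is 0.549 × 14.78 = 8.1 points on the review's SD, against the 0.52 said to be assumed: about 16 times larger.

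**The case against.** Several points can be made for the article, and some limit what may be said.

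*The review may report a pooled difference that is not the subtraction of the two quoted means.* The review is not available here, so this cannot be excluded. But the article prints these means as the foundation of the calculation, and subtraction is the only reading its text supports. The result is therefore a statement about the quoted figures.

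*The medium-effect sentence gives the true target.* It may, but it stands beside the other basis without replacing it, and it carries no number.

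*A reader might infer that the three-group F-test at f = 0.25 is the real basis.* The match with 159 is close, but nothing in the article says so, and other generic routes land nearby: a two-sided t-test at d = 0.55 also needs about 53 per arm, and a one-sided test at d = 0.5 with 53 per arm has 82% power. Only the sponsor can say which calculation was run.

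*A reader might infer that pairwise power for a medium effect is simply 72%.* That figure is for an unadjusted t-test on 53 per arm. Section 2.5 plans a covariate-adjusted mixed model and an intention-to-treat analysis of everyone allocated. At 75 per arm power is 86%; at 53 per arm with an assumed covariate correlation of 0.5 it is about 84%; at 45 per arm without adjustment it is 65%. This objection stands, so a range belongs in the text. It does not touch the 5% result.

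*A null result need not be misread*, since the article also speaks of a medium effect and describes the project as small in scale. That is fair: the misreading is a risk, not a certainty.

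**Conclusion.** Wrong as written. On the quoted figures (difference 0.52, pooled SD 14.78, d = 0.035), 53 per arm gives about 5% power at two-sided alpha 0.05, not 80%, and about 12,700 per arm would be needed. Neither the choice of sidedness, nor use of all 75 per arm, nor pooling of the intervention arms, nor any realistic covariate adjustment changes this. The medium-effect claim contradicts the stated basis.

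The conclusion rests on reading the average difference as the difference of the two quoted means. The values d = 0.5 and f = 0.25 are conventional assumptions used only to gauge what a medium effect might mean. The documents do not establish which calculation produced 159. Nor does this point show that 225 is the right enrolment: the paragraph's own 40% attrition leaves 45 per arm, below its stated minimum of 53.

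**What to change.** In section 2.2:

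1. Delete the statement that the calculation assumes the review's difference.
2. Have the sponsor state the effect size, test and sidedness actually used to reach 53 per arm. If it was a three-group F-test at f = 0.25, say so; the sponsor must confirm this.
3. Report the effect detectable at 80% power for each arm-versus-control comparison. Under an unadjusted two-sided t-test this is d = 0.55 at 53 per arm (72% power at an assumed d = 0.5) and d = 0.60 at 45 per arm (65% power). Note that covariate adjustment, or analysing all 75 per arm, would raise the power.
4. State that an effect as small as the quoted review difference cannot be detected, so a non-significant result is not evidence against it.

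The cost is the rewriting of one paragraph and a less favourable power statement. No added enrolment and no change to arms or procedures is requested.

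### The sample-size paragraph is wrong twice: 53 women per arm has about 5% power, not 80%, for the difference it cites, and 225 enrolled leaves 135 completers, not 159, at the stated 40% attrition

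*Protocol article*

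**What the plan says.** Section 2.2 (Sampling Details and Characteristics of the Sample) contains the article's only sample-size justification, in one paragraph.

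- Minimum size: "The minimum sample size for MAMH@WORK project will be 159, that is 53 women in each group".
- Enrolment: "Attrition rate is considered to be approximately 40% and thus, a total of 225 pregnant women, 75 in each arm, will be enrolled".
- Source values, from a literature review of psychological interventions to prevent postpartum depression: "mean depression scores (± standard deviation) of intervention and control groups of 11.00 ± 14.63 and 11.52 ± 14.93".
- Effect assumed: "These sample size calculations assume the average difference between intervention and control arms" in that review, "considering a 95% confidence interval and a 80% power of the test to detect a difference between depression scores of both arms".
- Closing claim: "This sample size allows for a medium effect size of the intervention to be detected for depression and anxiety scores". No number is attached to the word medium.

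Section 2.5 (Statistical Analyses) says that "the significance level will be set to α = 0.05". It plans an intention-to-treat analysis of everyone allocated, with last observation carried forward, and a per-protocol analysis of women who completed all evaluations. Effect sizes are to be taken from the per-protocol analysis only.

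**The concern.** The paragraph prints its inputs, its method and its results, and they do not fit together. A difference of about half a point against an SD near 15 is very small, yet it is said to be detectable with 53 women per arm. The last sentence then names a medium effect, which is more than ten times larger than the cited one. In addition, taking 40% off 225 does not leave 159.

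What is at stake is how the result is read. The stated 80% power does not exist for the difference on which the plan says it rests. The stated minimum is also missed under the plan's own attrition, and the planned effect-size estimates come from exactly that reduced set of completers.

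**Working it through.** **Inputs.** From section 2.2: means 11.00 and 11.52; SDs 14.63 and 14.93; power 80%; 53 per arm; 159 in total; 225 enrolled; attrition about 40%. The significance level is 0.05, from section 2.5 and from the 95% confidence interval in section 2.2. The test is taken as two-sided because sidedness is not stated.

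**1. Sample size from the stated basis**

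- Difference: 11.52 − 11.00 = 0.52.
- Pooled SD: √[(14.63² + 14.93²)/2] = √[(214.04 + 222.90)/2] = 14.78.
- Standardised difference: d = 0.52/14.78 = 0.035.
- Required n per arm: 2 × (1.960 + 0.842)² × (14.78/0.52)² = 12,684 (normal approximation, unrounded inputs). A one-sided test needs 9,991.

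The plan's 53 is not reproduced. Power for the 0.52-point difference under several readings:

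| Reading | Power |
|---|---|
| 53 per arm, two-sided | 5.4% |
| 53 per arm, one-sided | 7.2% |
| 106 (both intervention arms pooled) against 53 | 5.5% |
| Three-group ANOVA, N = 159 | 5.2–5.3% |
| 75 per arm (no attrition), two-sided | 5.5% |
| 45 per arm, two-sided | 5.3% |

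More generous readings do not reach 53 either. Treating the printed SDs as variances still requires 859 per arm. Adjusting for a baseline score with an assumed correlation of 0.99 still requires 253 per arm.

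**2. What does reproduce 159**

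A one-way ANOVA with three groups, f = 0.25, level 0.05 and 80% power needs N = 157.2, which is 53 per group or 159 in equal arms. Power at 159 is 80.5%. This agrees with the paragraph's closing reference to a medium effect. However, f = 0.25 is the conventional value and is assumed here; the article names neither ANOVA nor f as the basis of the calculation.

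**3. Attrition**

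- The plan's figure: 53 × 1.4 = 74.2, rounded up to 75; 75 × 3 = 225. This reproduces the enrolment target and suggests that 40% was added on.
- Inflation that keeps 53 completers: 53/(1 − 0.40) = 88.3, so 89 per arm or 267 in all. On the total, 159/0.60 = 265.
- Completers expected from the plan: 225 × 0.60 = 135, or 45 per arm.
- Attrition at which 225 leaves 159: 1 − 159/225 = 29.3%.
- Range around the stated rate: 35% leaves about 146, and 45% leaves about 124. Even 30% leaves 157.5.

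**4. Power for a medium effect, unadjusted comparison**

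d = 0.5 and f = 0.25 are conventional values, assumed because the article gives none.

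| Women per arm | Power, pairwise d = 0.5 | Pairwise d with 80% power | Power, omnibus f = 0.25 |
|---|---|---|---|
| 45 (completers at 40% attrition) | 65% | 0.60 | 73% |
| 53 (stated minimum) | 72% | 0.55 | 80% |
| 75 (all randomised) | 86% | 0.46 | 93% |

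**The case against.** The strongest reply is that the size is sensible and only its explanation is faulty: 159 is what a three-group comparison of a medium effect requires, and the last sentence says that a medium effect is the target. That is fair as far as it goes. It concedes that the stated basis is wrong, and it leaves the attrition step uncorrected.

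A second reply is that the intention-to-treat analysis includes all 225 women, so that 75 per arm applies. Nominally this gives 86% power for d = 0.5. It stands as a limit on the completer figures, which describe the per-protocol set and an unadjusted test, whereas section 2.5 plans a covariate-adjusted mixed model. But carrying the last observation forward does not restore lost final outcomes, effect sizes are reserved for the per-protocol set, and even 75 per arm gives only 5.5% power for the cited difference.

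A third reply is that attrition is only approximate. A rate near 29% cannot reasonably be called about 40%.

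Two stronger readings should be resisted.

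- A reader might infer that the printed SDs are impossible because they look too wide for the EPDS or HADS. The article does not say which scales lie behind the review's scores, a review may combine several, and the article gives item counts but no score ranges. The point is not supported and nothing here depends on it.
- A reader might infer that ANOVA with f = 0.25 is the basis actually used. The numerical match makes this plausible, but only the sponsor can confirm it.

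**Conclusion.** Both errors stand on the article's own figures.

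First, 53 per arm does not give 80% power for the cited difference. Power is about 5% two-sided, the required size is about 12,700 per arm, and none of the alternative readings tried closes the gap. The claim also conflicts with the closing sentence of the same paragraph.

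Second, 225 enrolled at 40% attrition yields 135 completers, 24 fewer than the stated minimum of 159.

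These conclusions assume a two-sided 0.05 level, and a one-sided test does not change them. The power figures for a medium effect rest further on conventional effect sizes and an unadjusted analysis of completers, so they are indicative. The documents do not show that the trial is too small for every purpose, nor that enrolment has to rise. They show that the printed justification is wrong and has to be restated.

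**What to change.** Rewrite the sample-size paragraph in section 2.2.

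1. Delete the statement that the number follows from the review's 0.52-point difference and its SDs.
2. Have the sponsor state the effect size, as a number, and the test actually used. If it was a three-group ANOVA with f = 0.25, say so.
3. State that 135 completers (45 per arm) are expected from 225 at 40% attrition. Give their power, labelled as an unadjusted per-protocol comparison: about 73% for omnibus f = 0.25, about 65% for a pairwise d of 0.5, and 80% for a pairwise d of about 0.60.
4. State that 159 completers requires attrition of about 29% or less. If 159 is a true minimum at 40% attrition, plan about 265 women, or 267 in three equal arms.

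Items 1 to 3 cost one reworded paragraph and a less favourable statement of power. The enrolment option in item 4 would add 40 to 42 women; whether to take it is the sponsor's decision.

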### 2.3. Description of the Intervention

The intervention will be developed in three phases: (1) a scoping literature review followed by a Delphi panel for consensus building on the contents and structure of a brief group CBT-based psychoeducation intervention, (2) the implementation and (3) effectiveness assessment of the intervention. In order to produce culture-specific recommendations for the intervention, Portuguese general practitioners, obstetricians, pediatricians, neurologists, psychiatrists, health and clinical psychologists, and nurses specialized in perinatal mental health care will be invited to take part in the Delphi panel, which will be informed by the scoping literature review.

The intervention will address maternal mental health and wellbeing protection and promotion during late pregnancy, postpartum and return to work. More specifically, it will target women’s psychosocial adjustment and resilience during this life stage, while promoting several strategic skills: recognition of signals and symptoms of mental disorders; reduction of stigma against mental disorders; coping skills for stressful situations, with a special focus on e-training of mindfulness; enhancement of help-seeking efficacy; and strengthening of emotional and cognitive self-regulation. It will follow a cognitive-behavioral and psychoeducational paradigm, and it is planned as a short-term group intervention of 20 h to be delivered in two blocks, one immediately before delivery and the other before returning to work. The first block will consist of two sessions, four hours each, whereas the second block will be organized into three sessions, four hours each. To better meet the objectives of this intervention, group size will not be larger than 15 women per session. Intervention block 1 will also include mindfulness exercises for coping with stress, and short videos with easy-to-follow exercises will be available at the private area of the website (details provided below). Block 2 will recap the main contents of block 1 and focus on resilience-promoting skills for the return to work. Women enrolled in the study will have access to e-mental health literacy materials (details provided below).

A standardized operation procedure (SOP) manual based on the literature reviews and expert consensus (Delphi panel) will be developed for healthcare professionals (i.e., trained psychologists and psychiatrists) and for the certified mindfulness coaches delivering the intervention. Sections to be covered in the SOP manual include: mental health literacy about mood and anxiety disorders; self- and perceived stigma towards mental illness; work–life balance; healthcare system accessibility; early signs of mental disorders; referral to mental health services and intervention options for treatment; mother–child interaction and promotion of secure attachment; social support guidelines; information about biofeedback, including technical details about the wearable devices, health benefits from combining biofeedback with brief group CBT-based psychoeducation interventions; and mindfulness concepts and exercises. With regards to the list of procedures to be used, these include group discussion of vignettes, discussion of illustrative cases (i.e., cases of PPD, poor and adequate mother–child interaction), emotional and cognitive expression exercises, video demonstration, roleplay of mother–child interactions, and demonstration followed by practical exercises on how to use biofeedback devices and interpret biofeedback outputs.

The RE-AIM (Reach, Effectiveness, Adoption, Implementation, and Maintenance) framework will be used to assess this evidence-based intervention in terms of its potential for translation and public health impact [68]. To assess the reach dimension of this project, the participation rate given as the proportion of invited pregnant women that accepted to participate in the intervention will be calculated. The effectiveness of the intervention will be assessed through a three-arm randomized controlled trial (Figure 1). The intervention group 1 will go through CBT-based psychoeducation sessions (including mindfulness e-training) by formally trained psychiatrists and psychologists; the intervention group 2 will benefit from the same CBT-based psychoeducation sessions (with mindfulness e-training) in addition to a biofeedback intervention; the control group will receive the care-as-usual from their health units. The development of a website for the project is planned and will include public and private areas. The public area will be accessible to the public and will contain information on mental health literacy, a description of the project’s objectives and its progress. Each participant allocated to the intervention arms will be provided with credentials to access her own private area. This area will contain personal, biomonitoring data (if applicable) and mindfulness e-training materials. Progressive Web Apps mimicking the website will be developed for smartphone use (Android and iOS).

Throughout the project, several physical and mental health outcomes will be measured and compared across groups. Since this intervention will be delivered by members of the research team, the adoption dimension (i.e., settings and staff that agree to deliver the intervention) does not apply in this case. However, the adequacy of the syllabus and a set of progress objectives (e.g., number of the psychoeducation intervention hours delivered, costs associated, and number of hours of online mindfulness exercises completed) will be used as a measure of its implementation. Finally, maintenance at both individual and setting levels will be measured at the last moment of data collection respectively by (a) the extent to which attendees maintain behavioral change after participating in the intervention and (b) the willingness of health unit managers to provide their users with this intervention.

Life events with potential confounding effects at the time of effectiveness assessment include becoming unemployed, diagnosis of cancer and life-limiting illnesses, newborn death, complications during delivery that severely impair mother and/or child, gestational diabetes, preeclampsia and eclampsia diagnosis, as well as losing the spouse, either by getting divorced or after death. See Statistical Analyses subsection for further details on how these will be handled.

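### Group delivery in both intervention arms makes the design partially nested, but the sample size does not allow for it and the stated MMRM names no session-group effect

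*Protocol article*

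**What the plan says.** Randomization is by individual woman: "Randomization will follow the minimization procedure [67] aiming for a balanced sample size for educational level and age groups at the baseline" (section 2.2).

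The programme is delivered in groups: "it is planned as a short-term group intervention of 20 h to be delivered in two blocks", as two four-hour sessions before delivery and three before the return to work, and "group size will not be larger than 15 women per session" (section 2.3). The procedures involve interaction between women: "these include group discussion of vignettes, discussion of illustrative cases", with roleplay among the others listed.

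Both active arms receive this; "the intervention group 2 will benefit from the same CBT-based psychoeducation sessions (with mindfulness e-training) in addition to a biofeedback intervention". By contrast, "the control group will receive the care-as-usual from their health units".

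On size, section 2.2 says "The minimum sample size for MAMH@WORK project will be 159, that is 53 women in each group", raised to 75 per arm (225) for attrition of about 40%. It cites means and standard deviations from a review, 95% confidence, 80% power and a medium effect. It gives no ICC, number of groups or design effect.

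On analysis, section 2.5 says "Mixed model repeated measure (MMRM) analyses will be used for the analyses of main and secondary outcomes, comparing between control and intervention groups", with adjustment for covariates that are still to be selected. No session-group or facilitator effect is named.

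**The concern.** Women who share sessions, discussion and roleplay may end up with outcomes more alike than those of women in different groups. This can happen in the two intervention arms and has no counterpart in the control arm, so the design is partially nested.

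A standard MMRM models the correlation between one woman's repeated measurements. It does not, without a further term, model correlation between women in the same session group. If that correlation is positive and left out, the standard error of an intervention-versus-control difference is too small, confidence intervals are too narrow and the test rejects too often. The trial also has less power than its sample size implies. A model term can be added later, but group membership that was never recorded is hard to recover, and the size of the trial is already fixed in this article.

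**Working it through.** **Inputs.** From the article: 53 per arm minimum, 75 per arm enrolled, about 40% attrition, group cap of 15, alpha 0.05, 80% power. Assumed, because the article gives none: ICC 0.02 to 0.05, and a group size m of 15 (the cap) or 9 (15 less 40%). Full groups would mean 75/15 = 5 groups per intervention arm.

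**Reproducing the stated size.** The cited means and standard deviations differ by 0.52 with pooled SD 14.78 (d = 0.035), which would need 12,684 per arm. They do not give 53, which is a separate matter. Reading the stated medium effect as f = 0.25 in a three-arm one-way ANOVA, alpha 0.05 and 80% power, gives a total of 157.2, rounded up to 53 per arm = 159. Of the calculations tried, only this one gives exactly 159, and it assumes independent women. The step to 75 is attrition alone: 53 × 1.4 = 74.2. Neither step leaves room for a design effect.

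**Formulas.** In an intervention arm the design effect is DE = 1 + (m − 1) × ICC. With equal arms, the true variance divided by the unadjusted variance is:

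- against control: R = (1 + DE)/2;
- between intervention arms, each group confined to one arm: R = DE;
- between intervention arms, sessions mixing both arms equally: the shared group effect cancels, so R ≈ 1 − ICC.

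Actual two-sided type I error of the unadjusted test = 2 × [1 − Φ(1.96/√R)].

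**Against control**

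| Women of the same arm per group | ICC | DE | R | Type I error |
|---|---|---|---|---|
| 9 | 0.02 | 1.16 | 1.08 | 5.9% |
| 9 | 0.05 | 1.40 | 1.20 | 7.4% |
| 15 | 0.02 | 1.28 | 1.14 | 6.6% |
| 15 | 0.05 | 1.70 | 1.35 | 9.2% |
| 7.5 (mixed sessions of 15) | 0.02 | 1.13 | 1.065 | 5.8% |
| 7.5 (mixed sessions of 15) | 0.05 | 1.325 | 1.1625 | 6.9% |

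A simulation with five arm-specific groups of 15 (20,000 runs) gave 6.6% and 9.7% at ICC 0.02 and 0.05, close to the formula. At ICC 0 the error stays at 5%.

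**Between the intervention arms**

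| Composition | ICC 0.02 | ICC 0.05 |
|---|---|---|
| Arm-specific, 9 per group | 6.9% | 9.8% |
| Arm-specific, 15 per group | 8.3% | 13.3% |
| Mixed | 4.8% | 4.4% |

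**Detectable effect and power against control.** For a two-arm comparison at two-sided 5% and 80% power (normal approximation, single time point), detectable d = (1.960 + 0.842) × √(2/n) × √R.

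| Retained | m | ICC 0 | ICC 0.02 | ICC 0.05 |
|---|---|---|---|---|
| 75 per arm | 15 | 0.46 | 0.49 | 0.53 |
| 45 per arm (75 × 0.6) | 9 | 0.59 | 0.61 | 0.65 |

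At the stated minimum of 53 per arm with m = 15, power for d = 0.5 falls from 0.73 at ICC 0 to 0.67 at ICC 0.02 and 0.60 at ICC 0.05.

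**The case against.** The strongest objection is that the analysis half is read from silence. Section 2.5 does not say that women are treated as independent. It names a model class and leaves the adjustment variables open. Random effects are commonly set in an analysis plan, which is not shown, and this is a condensed article. That objection stands: a reader might infer that the trial will ignore clustering, and the text does not establish it. It does not reach the sample size, which is stated here with its ingredients and no clustering allowance.

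Second, inflation needs a positive ICC, and none is given. At ICC 0.01 the error against control is only 5.5% (m = 9) to 5.8% (m = 15). Fifteen is a maximum, so the figures at 15 are an upper case. Both points stand.

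Third, a reader might infer that the contrast between the two intervention arms suffers most, because both arms are clustered. That holds only if each session group contains one arm. Section 2.3 says the second arm gets the same sessions plus biofeedback. Biofeedback demonstrations are among the listed procedures, which may hint at separate sessions, but nothing settles it. With mixed sessions the unadjusted test of that contrast is slightly conservative.

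Fourth, the article does not say that groups keep the same leaders, or that the same women stay together from the block before delivery to the block before the return to work. A single fixed group per woman is therefore itself an assumption.

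**Conclusion.** The point holds in conditional form. The article fixes a partially nested design and a sample size with no allowance for it, and the MMRM as described names no session-group effect. If none is fitted, type I error against control is above 5% for any positive ICC. For assumed ICCs of 0.02 to 0.05 the excess is modest to moderate: from just under 6% up to 9.2% at the cap with arm-specific groups. The stronger claim, that standard errors are already known to be too small and false positives are inflated in every contrast, is not supported. It would require a known positive ICC, a confirmed absence of a group term and, for the contrast between intervention arms, groups confined to one arm. This does not invalidate the trial, but it should be settled before the first sessions run, because it depends on data captured at that time.

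**What to change.** - **Record** each woman's session group separately for each block, and state whether groups contain one intervention arm or both.
- **Model:** add a random session-group effect for the two intervention arms to the MMRM, with control women as singletons, and use Kenward-Roger or Satterthwaite degrees of freedom. If groups are re-formed for the second block, use the group in force for the outcome being analysed, or a multiple-membership term.
- **Restate** the detectable effect or power for the planned 225 over ICC 0.02 to 0.05 and the expected group size. No additional enrolment is asked for.

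The cost is an identifier per block and one model term, or a somewhat more complex term if groups change between blocks. Intervals will be somewhat wider. With only about five groups per intervention arm if groups are full and arm-specific, the group variance will be estimated imprecisely, which is why the small-sample degrees of freedom matter.
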